Arm A (financial incentives): Participants will receive the usual standard care (same as control group), a loss-framed financial incentive, and weekly feedback on performance for 6 months.

Arm B (financial and social incentives): Participants will receive the usual standard care (same as control group), a loss-framed financial incentive, social incentives, and weekly feedback on performance for 6 months.

Arm C (control): Participants will receive standard care under the risk factor assessment and management programme (RAMP) including patient screening and education on diet, physical activity, and smoking conducted by a multi-disciplinary team ^18^.

The study will last for a total of 36 months including a 11-month suspension due to COVID-19 pandemic. This includes a 11-month recruitment period on rolling basis, 9-month follow-up period for each participant (consisting of 6-months intervention period and 3-month post-intervention period) and 3-month buffer for any rescheduling of follow-up. We plan to allow 4-months for the data analysis and 3-months to write-up our findings.

The pragmatic study design is based on the PRECIS-2 tool (Appendix 3) and RE-AIM frameworks.^19,20^ This trial is registered at ClinicalTrials.gov and will follow this pre-specified protocol.

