## Randomization

The random allocation process will be concealed from the front-line team, using tamper-proof methods, by way of pre-assignment based on a computer-generated sequence of random numbers administered by an independent research assistant. A sequence of random numbers will be generated prior to the start of the study by a statistician. To avoid baseline unbalance, we will stratify the randomization by age (30-49, 50-70) and sex. Computer software (R) will be used to generate the randomization sequence, using a block randomization structure with block sizes of 6 for the enrolment of participants.

The study will remain blind to laboratory and analysis staff. Research staff members at the designated study clinics who had no access to the randomization sequence will allocate a unique code to each of the participants based on their order of attendance. Because the allocation process will be concealed, the identity of the intervention groups will be unknown to the laboratory staff. The randomization codes will be masked from those assessing the outcomes and will only be revealed to the investigators after completion of the follow-up. A study statistician, uninvolved with other trial activities, will have access to the randomization codes for the purpose of conducting regular interim analyses and safety monitoring.

We will enrol 261 participants and randomly allocate each participant to one of the three study arms in equal proportion (1:1:1 ratio) (Figure 1). We assume 10% of participants do not complete the intervention or are lost to follow-up.

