## Stopping rule

Given that the study interventions are non-invasive and non-clinical, we do not plan to conduct any interim analyses to inform whether to continue the study. However, if we observe any SAEs confirmed by a physician where appropriate, we will terminate participation for the participant and conduct an immediate investigation while suspending the trial until a satisfactory resolution.

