# Statistical analysis

## Statistical methods

We compare sample characteristics between the arms using ANOVA for continuous variables, and Kruskal-Wallis test for categorical variables. The change from baseline HbA1c will be calculated for each individual participant. The time-matched change from baseline data will be analysed by a repeated-measure analysis of covariance (ANCOVA), fitting terms appropriate to the study design, including treatment group, time and group-by-time interaction. Participants will be included in the model as a random effect. Baseline values will be included as a covariate in the above models. Interim analysis will be performed after ~50% participants having completed the study. We will use the bootstrap method to resample participant groups 200 times to calculate the 95% confidence intervals. As a sensitivity analysis, we will use per protocol analysis to check for the robustness of our results. All analyses will be conducted using R statistical software.

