## Sample size justification

We propose to enrol 261 participants into our study. Based on published meta-analyses of clinical trials on the effect of lifestyle modification (diet and exercise interventions), we assume a mean difference of -0.6 in HbA1c with a standard deviation for each group of 1.5 percentage points.^12,13^ A sample size of 234 subjects (78 per group) will achieve 80% power to reject the null hypothesis of equal means between any two groups. The calculation is based on equal-variance t-test with a significance level of 0.05. We allow for a 10% dropout rate, giving the total target sample size of 261 (87 per group). Interim analysis will be performed after ~50% participants having completed the study. Sample size re-estimation may be applied based on interim look results upon the advice of our biostatistician. ​

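### The interim provisions disagree on number and purpose, and sample size may be changed on interim results with no stated rule, cap, blinding or error control

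*Protocol*

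**What the plan says.** Five places in the protocol bear on interim looks.

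- **Stopping rule:** "we do not plan to conduct any interim analyses to inform whether to continue the study".
- **Statistical methods**, repeated under Sample size justification: "Interim analysis will be performed after ~50% participants having completed the study".
- **Randomization:** a study statistician who takes no other part in the trial holds the codes "for the purpose of conducting regular interim analyses and safety monitoring".
- **Ethics:** an independent Data Monitoring Committee, with a biostatistician among its members, reviews safety and outcome data periodically. It is not linked to the look at half completion.
- **Sample size justification:** "Sample size re-estimation may be applied based on interim look results upon the advice of our biostatistician".

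The only significance level in the protocol is in the sample size paragraph: "The calculation is based on equal-variance t-test with a significance level of 0.05". On timing, Study Design states: "This includes a 11-month recruitment period on rolling basis, 9-month follow-up period for each participant". The same paragraph gives an 11-month pandemic suspension without saying where it falls relative to recruitment.

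**The concern.** A reader cannot tell how many looks there will be, what each is for, or who acts on it. One look and a regular series cannot both be the plan. The Data Monitoring Committee's biostatistician, the code-holding statistician and the biostatistician whose advice triggers re-estimation are not related to one another.

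The re-estimation sentence is the more serious part. It makes the final sample size depend on interim results at someone's discretion. If those results include the between-arm difference and the final test ignores this, the type I error exceeds its nominal level, and the final p-value and 95% interval lose their stated properties. That is hard to repair credibly once data have been seen. Separately, if the look comes after enrolment has ended, a re-estimation can be acted on only by reopening recruitment.

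**Working it through.** **1. The plan's own sample size.** Inputs (Sample size justification): difference 0.6, SD 1.5, power 80%, level 0.05 with sidedness not stated. Per group, n = 2(z₁₋α + z₀.₈₀)²(SD/difference)², with (1.5/0.6)² = 6.25.

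- One-sided 0.05: 2 × (1.645 + 0.842)² × 6.25 ≈ 77.3, so 78. The exact t-test gives 77.97, and power at 78 is 80.0%.
- Two-sided 0.05: 2 × (1.960 + 0.842)² × 6.25 ≈ 98.1, so 99 (100 by the t-test). Power at 78 is 69.9%.
- Dropout: 78/0.9 = 86.7, so 87 per group and 261 in total.

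The stated figure, "A sample size of 234 subjects (78 per group) will achieve 80% power", is therefore reproduced only with a one-sided 0.05 test. Error rates are shown below at one-sided 0.05 and at the conventional one-sided 0.025.

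**2. Worst-case type I error of an arm-level re-estimation with an unadjusted final test.** Take one contrast and no early rejection. Let z₁ be the stage 1 statistic and r the ratio of stage 2 to stage 1 size (the planned value for a half-way look is 1). With k the nominal critical value, the final test rejects when (z₁ + √r·z₂)/√(1+r) > k, so the conditional error under the null is

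1 − Φ((k√(1+r) − z₁)/√r).

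Maximising this over the permitted r for each z₁, and averaging over z₁ ~ N(0,1), gives the largest error that any rule could produce:

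| Permitted stage 2 size | Nominal one-sided 2.5% | Nominal one-sided 5% |
|---|---|---|
| 1 to 3 times stage 1 | 3.1% | 6.1% |
| At least stage 1, no upper limit | 4.3% | 8.2% |
| Free in both directions | 6.2% | 11.5% |

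The last row agrees with the closed form α + exp(−k²/2)/4: 0.025 + 0.1465/4 = 0.0616 and 0.05 + 0.2585/4 = 0.1146.

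**3. Timing.** Inputs: 261 participants, 11 months of recruitment, 9 months of follow-up each. Assume even accrual not split by the suspension.

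- Half (130.5) are enrolled at 11 × 0.5 = month 5.5 and finish 9 months at 5.5 + 9 = **month 14.5**, which is 3.5 months after recruitment closes.
- At month 11, only those enrolled in the first 2 months can have finished: 2/11 = 18%, about 47 people.
- If completion meant only the 6-month visit, the look would fall at 5.5 + 6 = month 11.5, still just after closure.
- A quarter (about 65) would have reached 6 months at 2.75 + 6 = month 8.75, before closure.

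**4. Effect of the suspension.** Suppose recruitment paused for 11 months after half were enrolled (month 5.5) while follow-up continued. Recruitment would then end at 11 + 11 = month 22, and the look at month 14.5 would precede closure. If the pause came before half were enrolled, half would be enrolled at 5.5 + 11 = month 16.5 and complete at month 25.5, again too late.

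**The case against.** Four stronger readings are tempting, and the protocol does not support them.

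- *The Stopping rule forbids any interim analysis.* It excludes only looks that decide whether to continue. A look used solely for re-estimation can stand beside it. The plain conflict is between one look and a regular series, with the purpose unreconciled.
- *Type I error is 8.3%, or 19.5% over three pairwise contrasts.* These are the figures for testing at 0.05 at both half and full information. They need an efficacy rejection at the interim, which no section allows. Moreover, 12.2% of the 19.5% already arises from three unadjusted contrasts at a single look, which is a separate matter.
- *The re-estimation is unblinded and the final test is at an unadjusted 0.05.* Neither is stated. The 0.05 belongs to the sample size calculation. Access to the codes and the reference to look results suggest arm-level data, but a blinded variance estimate is not excluded and would add little error.
- *The look falls after recruitment has closed.* This depends on accrual and on where the suspension falls, which the protocol does not say. The summary of changes also records recruitment sites added in September 2022.

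It is also fair to say that boundaries and re-estimation methods are often left to an analysis plan or committee charter, and that the table gives worst cases over all possible rules. What remains is not just missing detail: the sections disagree with one another, and the protocol itself grants an open permission tied to results.

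**Conclusion.** The concern holds in this form. The interim provisions do not agree on number or purpose, and the sample size may be changed on interim results with nothing stated to protect the error rate. How much harm follows depends on what is done. A blinded, variance-only re-estimation would cost little. One that uses arm-level data with an unadjusted final test could raise a one-sided 2.5% error to at most 3.1%, 4.3% or 6.2%, and a one-sided 5% error to at most 6.1%, 8.2% or 11.5%, according to how freely stage 2 may vary. These are upper bounds for a single contrast with a half-way look and no early rejection. The timing problem is conditional: with even accrual not split by the suspension, the look comes at about month 14.5, too late to guide an 11-month recruitment. The wording should be settled before any interim data are examined.

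**What to change.** 1. Make Randomization, Stopping rule, Statistical methods, Sample size justification and Ethics describe the same single interim. State its purpose, who sees unmasked data and who decides. Remove the reference to regular interim analyses, and keep safety tables for the Data Monitoring Committee as a separate item.
2. State that there is no between-arm efficacy look. If one is wanted, fix its boundary in advance (for example Haybittle-Peto, p < 0.001).
3. Replace the permission to act on interim look results with one blinded re-estimation from the pooled, arm-masked SD of 6-month HbA1c, upward only and with a stated maximum. A pre-specified method that uses arm-level data and controls the error rate would also cure the defect.
4. Trigger it on a number of 6-month results expected before recruitment closes, for example about 65 participants (25%), which is about month 9 under even accrual. State where the suspension falls, so that the timing can be checked.
5. State the sidedness of the test, because the re-estimation needs a defined starting point.

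The cost is protocol wording. The sponsor gives up an uncontrolled effect-based change in sample size, and the SD is estimated from fewer people. Its approximate relative standard error, 1/√(2(n−1)) under normality, is 1/√128 = 8.8% at n = 65 against 1/√258 = 6.2% at n = 130.

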# Direct Access to Source Data

The investigator(s)/institution(s) will permit trial-related monitoring, audits, IRB/REC review, and regulatory inspection(s), and provide direct access to source data/documents.

# Quality Control and Quality Assurance

Our research personnel will follow Good Clinical Practice (GCP) and our standard operating procedures to ensure proper conduct throughout the study. The trial will be conducted in strict compliance with the approved study protocol. Only trained phlebotomists or registered/enrolled nurses will collect blood samples. Other research personnel will also be trained and briefed to collect data, recruit participants, and answer questions from the participants or their family members.

# Ethics

The study will be conducted in compliance with this protocol, the Declaration of Helsinki ^29^, Good Clinical Practice, and the applicable regulatory requirements. In line with Good Clinical Practice guidelines, a Data Monitoring Committee will be established as an independent group consisting of biostatistician, clinician and person with expertise appropriate to the study at hand. The Data Monitoring Committee will meet periodically before and during the study to review data on safety and outcomes. Written informed consent will be obtained by our research staff directly from eligible participants after thoroughly explaining the study design, purpose and necessity of randomization to each potential participant. Rights and well-being of participants will be well protected during the whole study period, participation in the study is on a purely voluntary basis and participants are free to withdraw their consent and participation at any stage of the study with no explanation and without any prejudice.

Participants in the control arm will receive usual care. There are no major risks associated with the interventions. The process of collecting blood is associated with minimal risk, a small number of participants may have local reactions with the symptom of mild transient pain and bruising, but this will not influence their health. Another potential risk is loss of confidentiality due to data breach, but as the intervention and general physiological metrics do not carry large social stigma, these costs would be limited, and we will make every effort to control the risk. Participants in the study, as members of the whole society, will also benefit indirectly from this trial as the findings will make important contributions to our knowledge regarding public health strategies and inform evidence-based health policy for chronic diseases in Hong Kong, China, and elsewhere.

# Data Handling and Record Keeping

Qualtrics is a software application and workflow methodology designed to collect and manage data for research studies. Qualtrics is a secure, web-based applications designed to support data capture for research studies, providing: 1) an intuitive interface for validated data entry; 2) audit trails for tracking data manipulation and user activity; 3) automated export procedures for data downloads to Excel, PDF, and common statistical packages (SPSS, SAS, Stata, R); and 4) procedures for importing data from external sources.

Data for the questionnaire will be entered by the research staff directly to the Qualtrics electronic data capture system at the time of contact with the participants. All data obtained from the participants will be extracted into the secure Qualtrics database. This extraction will be facilitated by authorized researchers. The servers supporting the project database are secured by the University of Hong Kong in password-protected computers. All records will be entered using a personal identification code, making the records unidentifiable in Qualtrics. The link between the protected health information and personal identification code will be stored separately. All identifying data is anticipated to remain on the University of Hong Kong Qualtrics server in a locked cabinet in a locked room. Personal data will be protected in the database such that the personal data cannot be downloaded when the other anonymized study data are downloaded for analysis. The University of Hong Kong will have quality control check, tracking and cleaning of the data every week. Only fully deidentified data will be shared with researchers outside the study.

All data will be stored in the School of Public Health, HKU. All personal data will be kept confidential. Data from this study may be used in presentations and papers. Any potentially identifying information such as visit dates will not be shown.

# Financing

This study is supported by a GRF grant from the Research Grants Council of the Hong Kong Special Administrative Region, China.

# Publication Policy

The study will be published in international peer-reviewed journals. The results will be reported according to CONSORT guidelines.

